### Secondary outcome measures

Pain: Self-reported pain will be assessed using the VAS [27]. The VAS is a tool used to quantify the level of pain experienced by participants during the study period, with scores ranging from 0 to 10, where 0 indicates “no pain” and 10 indicates “unbearable pain.”

Disability: The Oswestry Disability Index (ODI) will be used to measure functional disability. This scale consists of 10 sections, each scored from 0 to 5 points, with higher scores indicating greater disability. The relative value will be expressed as the total score divided by the total possible score, multiplied by 100%. Participants will select the option that best describes their level of functional disability on the day of assessment.

Real-time ultrasound image (RUSI) Assessment of Muscle Thickness: The evaluation of muscle thickness will be conducted using the SONIMAGE HS1 (KONICA MINOLTA, Shanghai, China) equipped with a 65 mm convex array transducer (C5-2 type, frequency 5 MHz). For the abdominal muscles, participants will be positioned supine with their knees flexed at 90° and hips flexed at approximately 45°. The transducer will be placed gently at the intersection of a horizontal line passing through the umbilicus and a vertical line passing through the anterior superior iliac spine to visualize the TrA/IO. Measurements will be taken at the end of expiration. For the LM, participants will be positioned prone with a pillow placed under the abdomen to minimize lumbar lordosis. Using the sacrum as a reference, the probe will be positioned longitudinally over the spinous processes of L3, L4, and L5 and moved laterally to observe the LM at these levels to measure muscle thickness [28]. The muscle activation ratio will be calculated as follows:

$$Muscle\;Activation\;Ratio=\frac{Contracted\;Thickness}{Relaxed\;Thickness}$$

For the TrA, the preferred activation ratio will be calculated using the formula:

$$Preferred\;Activation\;Ratio\;=\frac{TrA\;Contracted\;Thickness}{(TrA\;+IO+EO)\;Contracted\;Thickness}-\frac{TrA\;Relaxed\;Thickness}{(TrA+\;IO\;+\;EO\;)Relaxed\;Thickness}$$

A higher value of the preferred activation ratio indicates a relatively greater change in the contracted thickness of the TrA, while a lower value suggests a relatively greater change in the contracted thickness of the EO and IO muscles [19].

Proprioception Testing: Proprioception will be assessed using joint repositioning error(JRE) as the primary outcome measure. Participants will be seated with their feet flat on the ground and hands resting on their thighs. The examiner will guide the participant into the neutral position of the lumbar spine. The measurement will start at the sacral level 1 (S1), with the center of a 10 cm measuring tape positioned at the measurement starting point. A laser pointer will be placed 50 cm behind the participant, aimed at the center of the 10 cm measuring tape located at S1. The examiner will instruct the participant to remember the target position, then perform two maximum anterior pelvic tilts and posterior pelvic tilts, holding each position for 5 seconds before returning to the neutral target position. The deviation from the starting point will be measured in centimeters as the JRE [29]. Prior to the assessment, participants will undergo two practice trials to familiarize themselves with the testing procedure. A total of three tests will be conducted, with a 1-minute rest between each test. The average of the absolute errors from the three measurements will be calculated to represent the magnitude of the error.

### Data collection and management

Data will be collected at baseline, at week 6, and during the 6-month follow-up. Throughout the training period, all data will be recorded and stored in case report forms (CRFs). Researchers will also contact participants via phone to ensure they complete follow-up assessments. If a participant fails to complete the assessment within two days of the scheduled date, they will receive a reminder phone call. At the conclusion of the trial, all research data will be extracted from the CRFs into Excel spreadsheets by two data managers who are blind to the group allocation. These data managers will have completed rigorous data monitoring training and will input the real-time data into the Chinese Clinical Trial Registry. After the data have been double-checked for accuracy, statisticians will conduct statistical analyses on the data. Since this study does not involve a drug trial, and the sponsors or funders will not have access to the raw data, there will be no establishment of a data monitoring committee, nor are there plans for trial audits. Additionally, due to the very low risk of adverse events and other unexpected impacts, this study will not conduct interim analyses, and no stopping guidelines have been formulated.

### Statistical analysis

Statistical analyses will be performed using SPSS Version 22.0 software (IBM). Continuous variables that conform to a normal distribution will be expressed as means ± standard deviations, while non-normally distributed continuous variables will be presented as medians (interquartile range). Categorical variables will be reported as proportions and rates. Baseline comparisons for continuous variables will be conducted using t-tests or non-parametric tests as appropriate, while baseline comparisons for categorical variables will utilize chi-square tests. For measurements taken at multiple time points, a mixed ANOVA will be employed to compare differences among groups and to analyze trends over time as well as interaction effects between treatment and time. In the presence of significant interaction effects between time and group, post hoc tests will be conducted with Bonferroni adjustments for multiple comparisons. The significance level will be set at 0.05 (two-tailed).

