### Sample size calculation

The sample size for this study is determined based on previous findings reported by Songjaroen et al [17]. The test statistic used to calculate the sample size was based on a mixed ANOVA. The calculation is based on the anticipated effect size for LM activation improvement, with a large effect size (Cohen’s dz = 0.7), a statistical power of 80%, a significance level of 5%, and a standard deviation of 0.05 points. Using G*Power 3.1 software for the analysis, it is calculated that at least 43 participants are required. Considering an anticipated dropout rate of 20%, a total of 52 participants will be recruited for the study (26 in the experimental group and 26 in the control group).

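### The mixed ANOVA treats baseline as a level of time and opens visit-specific comparisons only through a significant interaction; valid, but less powerful than a direct baseline-adjusted contrast

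*Protocol article*

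**What the plan says.** Under Data collection and management, the protocol article sets three visits: "Data will be collected at baseline, at week 6, and during the 6-month follow-up". Under Statistical analysis, for outcomes measured at several visits, "a mixed ANOVA will be employed to compare differences among groups and to analyze trends over time", together with the treatment-by-time interaction. The rule for going further is explicit: "In the presence of significant interaction effects between time and group, post hoc tests will be conducted with Bonferroni adjustments for multiple comparisons".

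No baseline-adjusted model is named. The only other stated use of baseline values is to test the arms against each other: "Baseline comparisons for continuous variables will be conducted using t-tests or non-parametric tests as appropriate". The level is 0.05, two-sided.

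The Sample size calculation section says the calculation was based on a mixed ANOVA, "with a large effect size (Cohen’s dz = 0.7), a statistical power of 80%, a significance level of 5%, and a standard deviation of 0.05 points", giving 43 participants, raised to 52 (26 per arm) for 20% dropout. The article does not rank week 6 above month 6 and does not say how participants with a missing visit are analysed.

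**The concern.** Randomisation makes the arms equal in expectation at baseline. Using baseline as an outcome level has three consequences.

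- The group main effect averages in a visit at which the true difference is zero.
- The interaction spreads its sensitivity over two degrees of freedom, when the clinical interest is the difference at a follow-up visit.
- The baseline value is not used as a covariate to remove between-person variance.

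The gate adds to this. If the interaction misses significance, no between-arm comparison at week 6 or at month 6 is planned. If it is significant, that comparison is made at a reduced level. At stake is power, and a clear estimate of the effect at a named time, in a trial of only 52 people.

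**Working it through.** **Inputs from the document.** Two arms of 26; three visits; alpha 0.05 two-sided; effect 0.7, read here as a between-arm difference in SD units.

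**Assumed, not in the document.** The effect is present at both follow-ups; compound symmetry with correlation rho = 0.3, 0.5 or 0.7; normal data; complete data unless stated.

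**1. The plan's own figure.** Take f = 0.7/2 = 0.35, three visits, and a group-by-time F test with noncentrality f²(N − 2)(3 − 1) on 2 and 2(N − 2) df. Power is 0.791 at N = 42 and 0.802 at N = 43. The stated 43 is therefore reproduced as a three-visit interaction test, which supports reading baseline as a level of time. The match uses inputs the article does not state (this noncentrality option, and the effect, which it labels dz, read as a between-group d).

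**2. Group main effect.** The expected difference is (0 + 0.7 + 0.7)/3 = 0.467, which is two thirds of 0.7. The SD of a three-visit mean is √((1 + 2rho)/3) = 0.730, 0.816, 0.894. The noncentrality 0.467 × √(26/2)/SD is 2.30, 2.06, 1.88, so power is 62%, 52%, 45%.

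**3. Interaction.** The differences (0, 0.7, 0.7) deviate from their mean by −0.467, 0.233, 0.233; the sum of squares is 0.327. Noncentrality is 26 × 0.327/2/(1 − rho) = 6.07, 8.49, 14.16 on 2 and 100 df.

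**4. Week-6 contrasts.** The standard error of a difference is SD × √(2/26) = SD × 0.277.

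- Change from baseline: SD = √(2(1 − rho)) = 1.183, 1.000, 0.775; noncentrality 2.13, 2.52, 3.26.
- Baseline-adjusted: SD = √(1 − rho²) = 0.954, 0.866, 0.714; noncentrality 2.65, 2.91, 3.53.
- The ratio of the variances, adjusted to change, is (1 + rho)/2 = 0.65, 0.75, 0.85.

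**5. Power.** The interaction is from the noncentral F (simulation gave 59/73/93). The contrasts are simulated, with a week-6 ANCOVA standing in for the week-6 contrast of the mixed model.

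| Test, 26 per arm | rho 0.3 | rho 0.5 | rho 0.7 |
|---|---|---|---|
| Interaction, 2 df | 58% | 73% | 92% |
| Interaction significant, and week-6 change contrast at 0.025 | 42% | 57% | 81% |
| Baseline-adjusted week 6, at 0.05 | 73% | 80% | 93% |
| Baseline-adjusted week 6, at 0.025 | 62% | 72% | 87% |

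**6. Sensitivity to month 6.** If the effect halves to 0.35 SD by month 6, the interaction noncentrality falls to 4.55, 6.37, 10.62 and its power to 45%, 60%, 83%. The baseline-adjusted week-6 contrast is unchanged. If the effect vanishes entirely, interaction power returns to the values in the table, because the pattern (0, 0.7, 0) has the same sum of squared deviations.

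**7. Type I error.** The simulated rate for the interaction under no effect is 0.050.

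**8. Fewer completers (conditional).** With 42 completing all visits (52 × 0.8 = 41.6), 0.7 SD at both follow-ups and rho = 0.5, the interaction has 63%, the gated change contrast 46% and the adjusted contrast 71% on the same 42 people. If 47 have week-6 data, the adjusted contrast has 76%.

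**The case against.** The strongest defence is that a group-by-time mixed ANOVA is a conventional and valid randomised comparison. The interaction is itself a test of treatment and is not gated; only the visit-specific follow-up is. The sample size reproduces as that interaction test, so the trial is arguably powered for what it will test. All of this stands. The dilution of the main effect also matters less, since nothing makes the main effect the deciding test.

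Four stronger readings may tempt a reader; the article does not support them.

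- *Participants missing a visit will be dropped.* Classical repeated-measures ANOVA in SPSS works on complete cases, so this would follow if that procedure is used. The article states neither the procedure nor the handling of missing data, and its silence is no finding. The efficiency argument holds on the same people, as step 8 shows.
- *The main question may never be tested.* The article does not make week 6 the main question.
- *The plan halves the power.* An unadjusted week-6 difference, gated and Bonferroni-corrected for three comparisons, has about 41% at rho 0.5, against 80% for the adjusted contrast. The article fixes neither that contrast nor the factor of three, and the 80% charges nothing for month 6.
- *The baseline tests bias the result.* They are uninformative after randomisation but do not alter the treatment estimate.

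**Conclusion.** The point holds as one of efficiency and targeting, not validity. Against the gated week-6 change contrast, the baseline-adjusted contrast gains about 31, 23 and 12 percentage points at rho 0.3, 0.5 and 0.7 (73 − 42, 80 − 57, 93 − 81). With alpha halved for two follow-ups it gains 20, 15 and 6 (62 − 42, 72 − 57, 87 − 81).

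Against the interaction alone, the gain at the full level is about 15, 7 and 1 points. It is larger if the effect partly fades by month 6. With alpha halved, the adjusted contrast leads the interaction only at rho 0.3 when the effect is constant. Even then the interaction does not say at which visit, or by how much, the arms differ.

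The sizes rest on the assumed correlations, the assumed month-6 effect, compound symmetry, and week 6 being named in advance. First-order autoregressive correlation gives the same ordering of the gated and adjusted contrasts.

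**What to change.** - Name one primary follow-up visit in advance, for example week 6, the end of treatment.
- Fit a linear mixed model to the week-6 and month-6 values with the baseline value as covariate, plus group, visit and group-by-visit, and an unstructured covariance. Include every randomised participant with any post-baseline value, in the assigned arm.
- Report the adjusted group difference at the primary visit with its 95% CI, tested directly and not conditional on the interaction.
- Take month 6 from the same model as secondary, or split alpha between the two visits.
- Drop the baseline significance tests; describe baseline by arm instead.

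The cost is small: the same data and the same software (SPSS has a mixed-model procedure). It is not wording alone, because a primary visit must be chosen and the Sample size calculation section, which rests on a mixed ANOVA, must be restated to match the new primary contrast.

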## Discussion

The treatment of NSLBP poses significant challenges, with a substantial proportion of patients continuing to experience symptoms despite receiving treatment. This ongoing issue may stem from a limited understanding of the mechanisms that initiate and sustain pain. The unique aspect of this study is the simultaneous use of NMES with active CSE, providing a quantitative analysis of the synergistic effects on the improvement of muscle structure, function, and proprioception in NSLBP. Objective assessment methods will comprehensively evaluate the activation patterns, thickness changes, and motor control ability of the deep lumbar muscles. Data will be collected at baseline, at the end of the 6-week intervention, and at a 6-month follow-up to reflect both short-term and mid-term effects, addressing the gap in long-term effect assessment in existing research. Literature indicates that 6 weeks of CSE can significantly improve pain levels and motor function in NSLBP patients, with notable improvements in core muscle thickness and activation capacity [5,6,13]. The muscle remodeling effects of NMES typically manifest within 4–6 weeks [30], and extending the intervention period further may increase patient dropout rates, reducing the feasibility of the study. The selected pulse width of 200 μs for NMES is consistent with previous research on optimizing parameters for deep lumbar muscle NMES, ensuring effective muscle recruitment while maintaining patient comfort [22,23]. This parameter minimizes the risk of activating superficial muscles, which may contribute little to core stability in patients with NSLBP. Additionally, the individualized progression of exercises ensures that each patient reaches optimal engagement in the treatment, while minimizing the risk of symptom exacerbation or maladaptive movement patterns.

This study employs sEMG technology to assess the activation patterns of deep core muscles such as the LM and TrA. Its high sampling rate and sensitivity help capture dynamic muscle changes, particularly in quantifying muscle activation timing differences, which further reveal motor control impairments in patients [31,32]. The anticipated improvements in sEMG outcomes include increased muscle activation, with NMES enhancing motor unit recruitment, leading to more consistent activation of the TrA and LM during movement. This is particularly important for individuals with NSLBP, as these muscles often fail to activate effectively during functional tasks. The protocol also aims to improve motor control through neuromuscular system retraining, enhancing proprioceptive feedback and muscle coordination. This will result in better lumbar stability during movement, reducing the risk of injury. Over time, improvements in these sEMG outcomes are expected to correlate with functional benefits, such as reduced pain, increased stability, and improved movement patterns, allowing individuals to perform daily activities with less discomfort and greater ease, potentially reducing pain recurrence.

Furthermore, RUSI will be used to precisely measure the thickness and dynamic changes of core muscles, with quantification of the thickness changes in the TrA, IO,EO and LM effectively reflecting muscle remodeling and the structural effects of the NMES+CSE intervention. JRE will be used to quantify proprioceptive function, serving as a key tool to assess sensory input dysfunction in NSLBP patients. Studies have shown that improvements in proprioception are significantly associated with pain relief and enhanced motor function [29]. This study innovatively combines NMES superimposed on CSE interventions with JRE assessments to quantify lumbar proprioception recovery and further explore the relationship between sensory input and motor output. Our goal is to provide robust evidence to inform the design of a more efficient and practical treatment for NSLBP patients.

### Dissemination

The findings of this study will be disseminated through publication in peer-reviewed international journals and presentations at national and international conferences. Participants involved in the study will also receive the research results via telephone or email.
